### Potential harms and patient safety

3.13

According to current literature, it is not to be expected that complications or harm will be caused by electrotherapy. The observed side effects of HTEMS were nervousness and sleep disorders.^[13,15]^ Nevertheless, we will monitor potential harms. Undesirable or adverse effects of electrotherapy will be registered by the study team. The study team reports the events in the CRF as soon as they become aware of the event. They are responsible to judge whether the adverse event is associated with the intervention. Stopping criteria comprise: dysesthesia, aggravation of symptoms, adverse events with the devices, incompatibility of the electrodes, progress of underlying disease, or any new upcoming exclusion criteria during the intervention. Additionally, after inclusion study participants get a telephone number of a study team member to report any adverse events or other concerns. There are no concomitant care and interventions that are prohibited—usual care will continue during the study period. Insurance for the study participants is provided. Study data will be locked and only the study team will have access. Included patients are anonymized with a study identification number.

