### Statistical analysis

3.19

Statistical analyses are elaborated in a prespecified statistical analysis plan. The primary endpoint is a change in the EORTC-QLQ-CIPN 20 score during the 8 weeks of intervention. For our primary endpoint, we will use an intention-to-treat analysis according to the CONSORT statement.^[19]^ Data that are missing at completely random (unrelated to any variable in the data set) or at random (related to some variable, but not to the outcome itself) will be imputed.^[25]^ If missing items in questionnaires exist, the patient's previous responses to the same item will be used.^[21]^ Further analyses will include a per-protocol analysis (primary and secondary outcomes) to test the consistency of intervention effects across important subgroups, for example, type of chemotherapy. Furthermore, we will analyze the intensity of intervention (compliance) and the effect on the primary endpoint (eg, comparison of infrequently and frequently use of device). A minimum use on 5 of 7 days per week is required. All tests are 2-tailed, and a 5% probability level is considered as significant. Statistical analyses are carried out after the end of the trial, with no interim analysis planned. All statistical analyses are performed with IBM SPSS Statistics 23.0.

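### Subgroup consistency is assigned to a per-protocol analysis, and frequent versus infrequent device use is compared as an effect; both rest on use after randomization, which worsening symptoms can reduce

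*Protocol article*

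**What the plan says.** All references are to the protocol article; the statistical analysis plan it mentions was not available.

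- **Primary endpoint, section 3.19:** "For our primary endpoint, we will use an intention-to-treat analysis according to the CONSORT statement".
- **Per-protocol and subgroups, section 3.19:** "Further analyses will include a per-protocol analysis (primary and secondary outcomes) to test the consistency of intervention effects across important subgroups". Type of chemotherapy is the example given.
- **Device use, section 3.19:** "we will analyze the intensity of intervention (compliance) and the effect on the primary endpoint (eg, comparison of infrequently and frequently use of device". The next sentence reads "A minimum use on 5 of 7 days per week is required".
- **Significance, section 3.19:** "All tests are 2-tailed, and a 5% probability level is considered as significant".
- **Stopping, section 3.13 (Potential harms and patient safety):** "Stopping criteria comprise: dysesthesia, aggravation of symptoms, adverse events with the devices", followed by further items.
- **Randomization, section 3.5:** 1:1 in blocks of 4, with taxane and platin among the stratification factors.

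**The concern.** Two analyses are given tasks that they cannot perform.

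First, consistency across chemotherapy types is a question about the difference between two treatment effects. It is answered by a treatment-by-type contrast among the randomized patients. Restricting the data to adherent patients answers a different question, and it gives up the protection of randomization in the comparison where patients are fewest.

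Second, the comparison of frequent with infrequent users is not randomized. A patient whose neuropathy worsens may stop and so fall below the use threshold. Low use is then partly a consequence of the outcome, and comparing outcomes by use can produce an apparent dose-response from an inert device. The article's Discussion adds another route. It says that taxane neuropathy typically improves after chemotherapy, while oxaliplatin symptoms may worsen for months. Use could therefore differ by chemotherapy type for reasons unrelated to the device.

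At stake are the statements on subgroups and dose. According to the Sample size section, the pilot is meant to improve assumptions about effect size for later work. A spurious dose-response or a distorted subgroup result would feed into that.

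**Working it through.** The plan gives no figure to reproduce: section 3.18 states that no formal sample size calculation was done, and no adherence rate or standard deviation (SD) is given. The calculations below show what the stated analyses would yield if neither device had any effect.

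**1. Use-frequency comparison, closed form.**

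Assumptions (not from the documents): change is standard normal, with higher values meaning worse. The worst 20% become low users with probability *a*, and the others with probability *b*.

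- Mean of the worst 20%: φ(0.842)/0.2 = 0.280/0.2 = 1.40 SD.
- Mean of the others: −0.280/0.8 = −0.35 SD.
- Share of low users: L = 0.2a + 0.8b.
- Mean of low users: 0.28(a − b)/L. Mean of frequent users: −0.28(a − b)/(1 − L).
- Gap in favour of frequent users: 0.28(a − b)/[L(1 − L)].

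| a / b | L | Gap | In points, at an assumed SD of 15 |
|---|---|---|---|
| 0.3 / 0.2 | 0.22 | 0.028/0.1716 = 0.16 SD | 2.4 |
| 0.5 / 0.2 | 0.26 | 0.084/0.1924 = 0.44 SD | 6.6 |
| 0.5 / 0.1 | 0.18 | 0.112/0.1476 = 0.76 SD | 11.4 |
| 1.0 / 0.1 | 0.28 | 0.252/0.2016 = 1.25 SD | 18.8 |

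The gap is zero when a = b. It is therefore caused entirely by the link between outcome and use.

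**2. Both analyses at the trial's size, by simulation.**

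From the documents: 50 patients, 1:1 (25 per arm), two-sided 5%. Assumed: no effect of device or use; 70% or 50% adherence at the mean outcome; where use depends on outcome, the log-odds of adherence change by 0.5 or 1 per SD. There were 6,000 trials per scenario, each tested with a t-test.

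| Link between worsening and use | Per-protocol arm contrast: bias; rejection | Frequent vs infrequent: gap; rejection |
|---|---|---|
| None | about 0; about 5% | about 0; 5% to 6% |
| Same in both arms | about 0; about 5% | 0.47 to 0.84 SD; 34% to 87% |
| In one arm only | 0.15 to 0.41 SD; 7% to 17% | 0.23 to 0.43 SD; 12% to 30% |
| Opposite directions in the two arms | 0.42 to 0.65 SD; 24% to 37% | 0.17 to 0.19 SD; 8% to 9% |

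Analysed as randomized, the same trials gave a mean difference of about 0 and rejected in 4.6% to 5.4% of cases.

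The two analyses fail in different ways. The use comparison is distorted even when selection is identical in the arms. The arm contrast is distorted only when selection differs between them. In the one-arm scenarios, selection was placed in the HTEMS arm and the bias favoured HTEMS; by symmetry, the same selection in the TENS arm would favour TENS.

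**3. Precision of the proper subgroup analysis.**

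Assume an even taxane/platin split, so 12.5 patients per arm and type on average. The standard error of the interaction is √(4/12.5) = 0.57 SD, and the 95% half-width is 1.96 × 0.57 = 1.11 SD. For the overall contrast, the half-width is 1.96 × √(2/25) = 0.55 SD. The interaction estimate is thus about half as precise.

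**The case against.** The per-protocol sentence is additive: it says what further analyses will include, and it covers the primary endpoint, which also has intention-to-treat. A reader might infer that secondary outcomes will be analysed per protocol only, since intention-to-treat is tied in the text to the primary endpoint. The document does not support that inference. Nothing excludes an intention-to-treat analysis of secondary outcomes, the unseen analysis plan may name one, and the article commits to CONSORT reporting. This objection stands.

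A reader might also infer that per-protocol results will favour HTEMS. That is not supported either. The comparator is another home device with the same schedule, and the stopping criteria are stated for electrotherapy without distinction by arm. With no device effect and equal selection in the arms, the arm contrast is unbiased. Different devices and unblinded participants make unequal selection plausible, but its size and direction are unknown.

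Nor can it be said that all the secondary results at risk are blinded measurements. The clinician-reported tests are blinded; quality of life is reported by participants who know their device.

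Finally, studying use fits the pilot's process objectives. Device read-outs and adherence rates are legitimate outputs, and the use comparison is listed among further analyses. That is true, and it is a reason to keep the analysis, but not to describe it as an effect. It may also be that the sentence merely compresses a per-protocol analysis and a separate subgroup analysis into one. Even so, as written it names the wrong tool for the stated purpose.

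**Conclusion.** The point holds on two counts: per-protocol is named as the means of testing subgroup consistency, and the comparison of frequent with infrequent users is framed as an effect. Both condition on use after randomization, which the protocol's stopping criteria link to symptom worsening.

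The use comparison is the more exposed. With no device effect, the spurious gap is 0.16 to 0.76 SD under moderate selection and 1.25 SD in the extreme case. These sizes rest entirely on assumed adherence; the conversion to points also assumes an SD of 15. They show what is possible and do not predict what this trial will find.

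The per-protocol arm contrast carries a conditional risk of unknown direction. It would be wrong to conclude that the main result is compromised, because the primary endpoint is to be analysed by intention-to-treat. With that protection, in a 50-patient pilot, this should be fixed but is not critical.

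**What to change.** In section 3.19, or in the analysis plan if it does not already say so:

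1. State that secondary outcomes and chemotherapy subgroups are analysed as randomized.
2. Assess consistency by the treatment-by-chemotherapy-type interaction, reported as an estimate with a 95% confidence interval, using the existing taxane/platin strata.
3. Keep the per-protocol analysis as a sensitivity analysis, and remove from it the task of testing consistency.
4. Report device use by arm. Present any relation between use and outcome as an exploratory, within-arm, baseline-adjusted association, and do not call it an effect.

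The cost is a few sentences and a few extra tables; no design change or additional data collection is needed. The drawback is that the interaction will be imprecise with 50 patients, with a half-width of about 1.1 SD even under an even split. It should be reported as an estimate, and a non-significant result should not be read as evidence of consistency.

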### Trial management and roles of study team

3.20

A Trial Steering Committee, consisting of a doctor in physical medicine, a training therapist, an oncologist, a general practitioner, and an expert in statistics, will supervise the trial. Their tasks provide overall supervision and ensure that the trial is conducted consistently. The Trial Steering Committee will discuss the protocol regularly every 6 weeks and at the end of the trial. This committee is further responsible to ensure adequate enrolment of participants, discuss modification or cessation of the trial as appropriate and reviews any case of reported undesirable effects.

## Discussion

4

This pilot study aims to evaluate the efficacy of home-based HTEMS in CIPN and to determine the feasibility of a further large-scale RCT. To date, little research on high-tone therapy in CIPN has been carried out, even if this approach is widely used in clinical practice. We suppose that a structured treatment regime with high-tone therapy can improve patient care and symptom management of CIPN. Based on clinical observations, the effect of HTEMS on symptoms of CIPN seems promising. Although CIPN affects many patients with cancer, evidence for an effective therapy is still lacking. We cannot completely rule out that the therapy response in this pilot study is different depending on the type of chemotherapy administered. Oxaliplatin and paclitaxel can have different effects regarding the temporal course and localization of symptoms. Nevertheless, we decided to include different groups of patients. One reason is that there is no mandatory relation between the effect of HTEMS and the administered substance. CIPN causes predominantly sensory symptoms; motor or autonomic symptoms are much less common. Typically, oxaliplatin induces an acute sensory neurotoxicity with rapid onset of cold-induced distal dysesthesia and/or paraesthesia. The symptoms occur mostly during or shortly after administration and are transient and mild. With prolonged oxaliplatin treatment, a cumulative sensory peripheral neuropathy develops causing superficial and deep hypaesthesia and functional impairment. Furthermore, oxaliplatin affects hands more severely than feet.^[2]^ Neuropathy caused by taxanes develops cumulatively over time and typically improves after chemotherapy cessation. Oxaliplatin-related symptoms, in contrast, may get worse for several months after stopping chemotherapy, a phenomenon called “coasting-effect.”^[2]^ In this pilot study, we will include only patients with persisting CIPN 4 to 24 weeks after finishing the neurotoxic chemotherapy to exclude patients with spontaneous remission of sensory neuropathy.

## Conclusion

5

In daily clinical routine, good results have been achieved with the application of electrotherapy for CIPN. This pilot study can provide important evidence about the therapeutic effects of home-based HTEMS in CIPN, which is a worldwide concern in oncologic patients. Since HTEMS has hardly any side effects, it seems to be a promising approach in the therapy of CIPN.
